## Abstract

**Background:**

Postoperative delirium (POD) is a complication after surgery which leads to worse outcomes. The frequency of this syndrome is increasing as more elderly patients undergo major surgery. The frequency is around 10–25% but reaches as high as 50% for cardiac surgery. Although intranasal insulin (INI) administration of up to 160 units in patients with cognitive dysfunction and delirium has been shown to improve memory function and brain metabolism without complications such as hypoglycemia, it remains unknown whether INI prevents POD after cardiac surgery

**Methods:**

A multicenter, double-blind, randomized, controlled trial will be conducted at University of Tsukuba Hospital and Tsukuba Medical Center Hospital, Japan, from July 1, 2023, to December 31, 2025. A total of 110 elderly patients (65 years old or older) undergoing cardiac surgery requiring cardiopulmonary bypass will be enrolled and randomly allocated to intranasal insulin or intranasal saline groups. The primary outcome is the incidence of POD within 7 days after surgery. Secondary outcomes include days and times of delirium, screening tests of cognitive function, pain scores, duration of postoperative tracheal intubation, and length of ICU stay.

**Discussion:**

The present objective is to assess whether 80 IU INI administration during surgery prevents POD after cardiac surgery. The results may provide strategic choices to prevent POD in patients with cardiac surgery requiring cardiopulmonary bypass.

**Trial registration:**

The trial was registered with the Japan Registry for Clinical Trials with identifier jRCTs031230047 on April 21, 2023.

## Administrative information

Note: the numbers in curly brackets in this protocol refer to SPIRIT checklist item numbers. The order of the items has been modified to group similar items (see http://www.equator-network.org/reporting-guidelines/spirit-2013-statement-defining-standard-protocol-items-for-clinical-trials/).

## Introduction

### Background and rationale {6a}

Postoperative delirium (POD) is a complication after surgery in which acute disturbances of consciousness, attention, and perception appear and show diurnal fluctuations, resulting in impaired attention/thought processes and circadian rhythm disturbances [1]. This syndrome is increasing as more elderly patients undergo major surgery [2, 3]. The frequency is 10–25% [4, 5] but reaches as high as 50% for cardiac surgery [6].

Delirium is a short-term disease concept but has been shown to worsen long-term prognoses with increased lengths of hospital stay, postoperative complications, and mortality [7, 8]. Many patients with POD suffer mid-to-long-term postoperative neurocognitive dysfunction (cognitive dysfunction detected postoperatively in the absence of impaired consciousness using neuropsychological testing) [9], which leads to serious deteriorations in quality of life, such as an inability to work [10]. However, there is no standard prophylaxis for POD because pharmacological interventions, mainly anti-inflammatory, have not shown effective results in preventative treatment [11].

The precise mechanism of POD pathogenesis remains unknown but the neuroinflammatory response theory is the most likely explanation. Systemic inflammation induced by surgery and anesthesia causes acute brain inflammation [12]. In cardiac surgery, strong neuroinflammation is particularly induced by cardiopulmonary bypass (CPB), median sternotomy, myocardial ischemia-reperfusion injury, and various anesthetic agents [6], with these surgical factors thought to contribute to the high rate of delirium.

Intranasal insulin (INI) administration of up to 160 units in patients with cognitive dysfunction and delirium has been shown to improve memory function and brain metabolism [13–16] without hypoglycemia [17]. Glucose-insulin-normoglycemia therapy (high-dose intravenous insulin) [18] preserves short- and long-term memory after cardiac surgery [19] by suppressing inflammation in the brain due to insulin spilling over into the cerebrospinal fluid [20]. Insulin signaling in the brain was associated with cognitive function and perioperative inflammatory responses. Therefore, INI could be exploited to reduce POD and/or cognitive dysfunction.

### Objectives {7}

The objective is to determine whether preoperative INI administration reduces the incidence of POD in elderly patients undergoing cardiac surgery requiring cardiopulmonary bypass. In addition, the effects on cognitive function in the early postoperative period will be evaluated.

### Trial design {8}

This is a prospective, parallel-arm, double-blinded, randomized controlled trial. Consenting patients will be randomly assigned into the insulin or saline groups (1:1 allocation).

## Methods: participants, interventions, and outcomes

### Study setting {9}

The study will be conducted in the University of Tsukuba Hospital (academic hospital), Ibaraki, Japan, and Tsukuba Medical Center Hospital (tertiary hospital), Ibaraki, Japan.

### Eligibility criteria {10}

#### Inclusion criteria

Patients undergoing scheduled cardiac surgery using CPBPatients who are 65 years of age or older at the time consent is obtainedPatients with no history of nasal surgeryPatients who have given informed, written consent for this clinical research

#### Exclusion criteria

Patients with preoperative deliriumPatients with a score of 23 or less on the preoperative Japanese version of mini-mental state examination (MMSE) [21, 22]Patients scheduled to have hypothermia (32 degrees or lower) during surgeryPatients with a history of serious insulin allergyPatients with severe psychiatric disorders (depression, bipolar disorder, schizophrenia, etc.)Patients with obvious neurological diseases (Alzheimer’s disease, Parkinson’s disease, epilepsy, cerebral infarction, cerebral hemorrhage, etc.)Patients with severe visual or hearing impairmentPatients who have difficulty communicating in JapanesePatients deemed inappropriate by the principal or sub-investigators

### Who will take informed consent? {26a}

The research team members will invite eligible patients to participate in this study. The researchers (licensed medical doctors) will instruct them on the study protocol and obtain informed consent from all participants one to 60 days before surgery.

### Additional consent provisions for collection and use of participant data and biological specimens {26b}

Blood sampling (5 mL) will be performed just before surgery and at postoperative day 1, with samples preserved for a future study if patients consent to it.

## Interventions

### Explanation for the choice of comparators {6b}

INI may prevent POD because INI improves cognitive function in patients with cognitive impairment without causing hypoglycemia probably due to an anti-inflammatory effect described in the Introduction section.

There is currently no standard drug therapy to base protocols on, necessitating a de novo approach with established precedence from translational and clinical reports. As such, using placebo as a control is ethically acceptable.

### Intervention description {11a}

#### Anesthesia management

Medications on the day of surgery should be used only as necessary for anesthetic and perioperative management. In principle, hypoglycemic drugs should be discontinued but, if necessary, there are no restrictions on such medications, including diabetic drugs and drugs that may affect blood glucose levels (e.g., steroids),

Anesthesia care includes the use of the following monitors: a blood pressure monitor, electrocardiogram, oxygen saturation monitor, cerebral near-infrared spectroscopy monitoring and bispectral index monitor, and arterial catheter placed in the radial artery. After induction of anesthesia and tracheal intubation, a transesophageal echocardiography device will be inserted and a central venous catheter and pulmonary artery catheter will be placed through the right internal jugular vein.

Anesthesia methods are not specified and standard general anesthetics are to be used. In principle, extracellular fluid with 1% or less glucose content should be used as intravenous fluid but artificial colloid fluid, albumin, and blood products should be used as appropriate in case of decreased circulating plasma volume or hemorrhaging. Red blood cell transfusions will be used, if necessary, to achieve a hematocrit of at least 25%.

Before CPB, 300 IU/kg intravenous heparin should be administered followed by possible additional doses to keep the activating clotting time at 400–480 sec or longer. Protamine will be administered for heparin reversal after separation from CPB. During CPB, the pump flow rate should be 2.4 L/min/m^2^, the mean blood pressure should be 50–70 mmHg, and the body temperature should be maintained at 32–36 °C. Cardioplegia will be administered to initiate and maintain cardiac arrest.

A systolic blood pressure of 100 mmHg should be maintained before and after weaning from CPB with noradrenaline and dopamine used as needed.

If hypoglycemia (< 70 mg/dL) or hypoglycemia is strongly anticipated, a 20% glucose solution should be administered intravenously until normoglycemia is established. In principle, when blood glucose is >180 mg/dL, intravenous insulin will be administered to achieve a target blood glucose level of 70–180 mg/dL.

#### Study drug administration

After induction of anesthesia, the principal investigator or a staff investigator will administer the study drug intranasally into the right and left nasal cavities using a spray bottle.

##### Placebo group

After induction of anesthesia, the control drug (saline solution, Terumo Corp, Tokyo, Japan) will be administered into the left and right nasal cavities in 4 pushes each (0.1 mL per dose), for a total of 8 pushes.

##### Insulin 80 units group

After induction of anesthesia, the test drug (Humulin R, Eli Lilly Japan, Kobe, Japan) will be administered into the left and right nasal cavities in 4 pushes each (0.1 mL per dose), for a total of 8 pushes.

#### Criteria for discontinuing or modifying allocated interventions {11b}

When cardiac surgery is canceled or postponed and cannot be started within 60 days from the date of registrationDevelopment or presence of severe preoperative laboratory abnormalities (renal dysfunction, hepatic dysfunction, etc.)When it is found that the eligibility criteria are not met after enrollmentWhen the research enrollee withdraws consentWhen it is difficult to continue the study due to adverse events, etc. within 7 days after surgeryWhen it is difficult to continue the study due to worsening of complications within 7 days after the surgeryWhen the investigator determines that discontinuation is appropriate for other reasonsWhen this clinical research as a whole is terminated

#### Strategies to improve adherence to interventions {11c}

Not applicable. Interventions in this study will be completed during general anesthesia and without the patients’ cooperation.

#### Relevant concomitant care permitted or prohibited during the trial {11d}

There are no restrictions regarding concomitant care during the trial.

#### Provisions for post-trial care {30}

All study participants receive standard care. This includes extended follow-up after study participation has ended, if deemed necessary by the treating physician. According to the provisions of the compensation agreement, the investigator will compensate the participant for physical damage caused by the clinical trial intervention through compensation insurance.

## Outcomes {12}

### Primary endpoint

Incidence of delirium within 7 days after surgery. Delirium will be evaluated for 7 days after cardiac surgery. During the intensive care unit (ICU) stay, the Confusion Assessment Methods for the Intensive Care Unit (CAM-ICU) [23, 24] will be conducted twice a day for each patient. In wards, the newly developed 3-min diagnostic assessment for delirium using the Confusion Assessment Method (3D-CAM) [25] will be conducted once a day for each patient.

A patient is considered to have delirium if he/she tests positive for delirium at least once during the postoperative period.

#### Secondary endpoint

Number of days with deliriumNumber of times the patient has deliriumChange in MMSE-J between preoperative and 7 postoperative dayChange in the Japanese version of Montreal cognitive assessment (MoCA-J) [26, 27] between preoperative day 1 and postoperative day 7Pain score numerical rating score (NRS) [28]Length of postoperative tracheal intubationLength of ICU stay

## Participant timeline {13}

The participant timeline is presented in Fig. 1.

**Fig. 1 Fig1:**
[figure not shown]
Participant timeline. D, postoperative day; MMSE, mini-mental state examination; NRS, numerical rating scale

### Sample size {14}

In a study conducted at the University of Yamanashi Hospital, 33% of patients were in the placebo group and 9.5% in the insulin group (unpublished data, jRCTs031200290). Although that previous study differs from the present study in that it excluded patients aged 20 years or older undergoing cardiac or major vascular surgery using cardiopulmonary ventilation and patients with severe renal dysfunction, the incidence of delirium seems reasonable.

Based on this, if the delirium rates in the placebo and insulin groups are 33% and 10%, respectively, with two-sided a significance level of 0.05 on both sides and a power of 0.8, the number of cases per group would be 49. We will recruit 55 cases per group for a total of 110 cases, taking into account 10% dropout cases.

### Recruitment {15}

Patients will be informed in detail of the course of the study, all study procedures, potential risks, and the benefits of each intervention 1–60 day(s) before surgery. Patients will be recruited at the University of Tsukuba Hospital and Tsukuba Medical Center Hospital.

## Assignment of interventions: allocation

### Sequence generation {16a}

Randomly assigned sequences will be generated using an electronic data capture (EDC) system (UHCT ACREeSS, https://plaza.umin.ac.jp/UHCTA/acress/). Eligible participants will be randomly assigned to the insulin or saline groups in a 1:1 ratio. Patients will be stratified and assigned to the University of Tsukuba Hospital and Tsukuba Medical Center Hospital.

### Concealment mechanism {16b}

During enrollment by the investigator, the EDC system (UHCT ACReSS, https://plaza.umin.ac.jp/UHCTA/acress/) will assign each participant a randomization number.

### Implementation {16c}

The pharmacy will hand out coded study medication (insulin or saline) to investigators before surgery. Concealment is ensured by a randomization list which is held by the pharmacy only. This list contains the randomization numbers and the assigned treatment groups.

## Assignment of interventions: blinding

### Who will be blinded {17a}

Trial participants, treating surgeons, and outcome assessors will be blinded to the treatment assignment. The principal investigator shall remain unblinded to detect and treat adverse events immediately. Therefore, the principal investigator shall not assess postoperative outcomes.

### Procedure for unblinding if needed {17b}

The pharmacy will hold the unblinding codes. In case of medical necessity or emergency related to the procedure, the principal investigator has the power to unblind and inform the patient and attending medical staff.

## Data collection and management

### Plans for assessment and collection of outcomes {18a}

Research data will be collected in an EDC system using ACReSS (UHCT ACREeSS, https://plaza.umin.ac.jp/UHCTA/acress/).

The following data will be collected:

EnrollmentDemographic data (sex, date of birth, race, height, weight, history of illness, medical history of primary illness, comorbidities, smoking history, medications, allergy history, previous surgical history, EuroScore II [29])Laboratory and instrumental examinationsDelirium test: 3DCAMCognitive function screening tests (MMSE-J and MoCA-J)Pain scale: NRS

During surgeryBlood glucose: Measured 20 min after study drug administration. If glucose trends downwards, measurement will be continued every 10 min and glucose solution will be administered if necessary until normoglycemia is achievedSurgical data: Duration of surgery, anesthesia time, blood loss, volume of infusion, volume of blood transfused, urine output, minimum body temperature during CPB, duration of CPB, vasoactive drug use at discharge, fentanyl use, and remifentanil use

After surgeryLaboratory and instrument examinationsDelirium tests: CAM-ICU or 3DCAMCognitive function screening tests (MMSE-J and MoCA-J)Adverse eventsPain scoring: NRS

### Plans to promote participant retention and complete follow-up {18b}

During the preoperative visit, researchers will explain the procedure of intraoperative management and postoperative follow-up in detail. The research team will conduct an assessment of the participants with careful consideration of their individual statuses.

### Data management {19}

An electronic clinical management system (ACReSS, University Hospital Clinical Trial Alliance, Chiba, Japan) will be used. Patient data are stored in raw medical records at each hospital and anonymized EDC. Research data is stored at the Department of Anesthesiology, University of Tsukuba Hospital, for 10 years after completion of the study. Changes in EDC are preserved with a log showing the information of who made changes and when.

### Confidentiality {27}

All patient data are anonymized in the EDC system. Only study investigators, who are given an original ID and password, may access the EDC and input data on patients at their facility.

### Plans for collection, laboratory evaluation and storage of biological specimens for genetic or molecular analysis in this trial/future use {33}

Blood sampling (5 mL) will be performed at just before surgery and postoperative day 1, with samples preserved for a future study if patients consent. The blood will be stored in a – 80 °C freezer at the Department of Anesthesia, University of Tsukuba Hospital.

## Statistical methods

### Statistical methods for primary and secondary outcomes {20a}

#### Primary endpoint

The incidence of delirium within the first postoperative week for each group will be determined. The ratio of the incidence rate in the insulin group versus the placebo group and its 95% confidence interval will be determined.

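### Randomisation is stratified by hospital but the stated primary risk ratio has no hospital term, so its interval is slightly conservative if the hospitals differ; a minor, nearly free improvement

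*Protocol article*

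**What the plan says.** - **Protocol article, Sequence generation {16a}:** "Patients will be stratified and assigned to the University of Tsukuba Hospital and Tsukuba Medical Center Hospital". Allocation is 1:1. Hospital is the only stratification factor named.
- **Protocol article, Statistical methods {20a}, Primary endpoint:** the incidence in each group is obtained first, and then "The ratio of the incidence rate in the insulin group versus the placebo group and its 95% confidence interval will be determined". The section names neither hospital nor a method for the interval.
- **Protocol article, Sample size {14}:** the trial is sized as a plain comparison of two proportions, "if the delirium rates in the placebo and insulin groups are 33% and 10%, respectively", with "two-sided a significance level of 0.05 on both sides". The result is "a power of 0.8, the number of cases per group would be 49", raised to 55 per group for dropout. Hospital plays no part here either.

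**The concern.** Stratified randomisation balances the arms within each hospital. If hospital predicts delirium, this removes the between-hospital component from the true sampling variance of the treatment comparison. An analysis that ignores hospital still counts that component in its standard error. The interval is then wider than it need be, and the test rejects less often than its nominal level. At stake is a little precision that the design has already secured.

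A second, smaller point concerns scale. The sample size comes from a test on the difference in proportions, while the result is to be reported as a ratio with an interval. If significance is judged by whether that interval excludes 1, power depends on how the interval is built, and the section does not say.

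**Working it through.** **Inputs from the documents:** placebo 33%, insulin 10%, two-sided 0.05, power 0.8, 10% dropout (Sample size {14}); 1:1 allocation and two hospital strata (Sequence generation {16a}).

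**Assumptions, because the documents give no figures:** each hospital's share of patients, each hospital's placebo risk (averaging about 33%), and a common risk ratio of 0.10/0.33 = 0.303.

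**Step 1. The plan's own figure.** Pooled chi-square formula without continuity correction, mean risk 0.215:

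n = [1.96·√(2·0.215·0.785) + 0.8416·√(0.33·0.67 + 0.10·0.90)]² / 0.23² = (1.1387 + 0.4694)² / 0.0529 = 48.9, so 49.

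Dropout: 49/0.9 = 54.4, so 55. Both stated figures reproduce.

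**Step 2. Point estimate.** With equal arms in every hospital, the Mantel-Haenszel weights are 1/2 in each stratum. The stratified ratio is then (total insulin events/2) / (total placebo events/2), which is the crude ratio. Only the standard error changes, so there is no bias.

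**Step 3. Rejection rate under no effect** (nominal 5%; 98 patients, 50/50 hospital split, 200,000 simulated trials per row):

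| Hospital gap in risk | Crude Wald log-ratio interval | Mantel-Haenszel ratio interval | Crude chi-square | Cochran-Mantel-Haenszel |
|---|---|---|---|---|
| 0 points | 4.3% | 4.3% | 4.8% | 4.9% |
| 20 points | 3.8% | 4.2% | 4.3% | 5.0% |
| 30 points | 3.2% | 4.3% | 3.7% | 5.0% |

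The crude methods become conservative as the gap grows. The stratified ones stay where they were.

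**Step 4. Power from stratifying alone**, comparing like with like (49 per group, risk ratio 0.303, 400,000 simulated trials):

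| Placebo risks (patients per arm, by hospital) | Ratio interval: crude to stratified | Test: chi-square to Cochran-Mantel-Haenszel |
|---|---|---|
| No gap | 78.4 to 78.1% (-0.3) | 81.9 to 81.4% (-0.5) |
| 27% / 47% (35/14) | 78.3 to 78.5% (+0.2) | 81.9 to 82.0% (+0.1) |
| 25% / 53% (35/14) | 79.0 to 79.7% (+0.7) | 82.5 to 83.2% (+0.7) |
| 20% / 53.5% (30/19) | 79.5 to 81.0% (+1.5) | 82.9 to 84.5% (+1.6) |

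In width, the interval expected from the design rates uses SE(log ratio) = √(1/4.9 - 1/49 + 1/16.17 - 1/49) = 0.474, which gives 0.120 to 0.768. Stratifying with a 20-point gap (50/50 split) gives 0.121 to 0.762.

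**Step 5. Choice of interval, no hospital assumption needed.** Exact power at 33% versus 10% with 49 per group:

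- Pearson chi-square: 82.0%.
- Wald interval for the log ratio excluding 1 (a zero cell counted as a failure): about 78.5%.

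The Wald interval first reaches 80% at 52 per group (80.5%). If all 55 per group are evaluable it has 83.5%.

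**The case against.** The strongest reply is that the point rests on silence. The primary endpoint section does not call the ratio crude or unadjusted, and it names no Wald interval. This is a condensed article, and adjustment for stratification factors and the interval method are often left to an analysis plan, which is not shown. That stands as a limit: the crude reading is an inference. But the section does state an estimate and an interval, the sample size is built the same way, and the one factor used to randomise appears in neither. Asking for that stated method to be aligned with the design is fair.

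It is also fair that both hospitals share eligibility criteria, bypass management and delirium tests, and that cases with planned hypothermia are excluded to make the procedures alike. Nothing in the documents suggests a gap of 28 points or more. With smaller gaps the effect is negligible, and with none, stratifying costs a little power.

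A reader might infer that ignoring hospital costs 4 to 5 points of power. That figure appears if a crude Wald interval is set against a stratified score or Cochran-Mantel-Haenszel test (78.9 versus 83.2%, and 79.4 versus 84.5%, in the two widest-gap scenarios). The comparison changes two things at once, and most of the difference is Wald against score. With no hospital gap at all it still shows about 3 points (78.5 versus 81.5%), which cannot come from ignoring hospital.

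**Conclusion.** The point holds as a minor one. As written, the primary analysis does not use the factor by which patients were randomised, and its interval is conservative to the extent that hospital predicts delirium. The gain from stratifying is at most about 1.5 points of power in the scenarios of Step 4, close to nothing at a 20-point gap, and slightly negative with no gap. All of this depends on assumed hospital risks and shares.

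The interval method matters more: about 3.5 points (82.0 - 78.5), but only if the unnamed interval is the Wald one and significance is judged by it.

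Three stronger readings are not supported:

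- **Invalid result.** The estimate is unbiased under balanced allocation, and type I error falls rather than rises.
- **Wrong sample size.** Both 49 and 55 reproduce, and a ratio and a difference test the same null of equal risks.
- **An undefined ratio as a practical threat.** At 10% risk and 49 patients, the chance of no events is 0.9^49, about 0.6%.

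**What to change.** In Statistical methods {20a}, Primary endpoint, state: the primary estimate is the risk ratio for delirium stratified by hospital (Mantel-Haenszel), with a stratified score-type 95% confidence interval (for example Miettinen-Nurminen) and a Cochran-Mantel-Haenszel test at two-sided 0.05; the crude ratio is reported as descriptive. If an analysis plan already says this, a cross-reference is enough. Settle the wording before unblinding, so that the choice cannot follow the results.

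The cost is one sentence. Hospital is already recorded for randomisation, so no patients or data are added and the sample size stands. The downside is a power loss of no more than about 0.5 points if the hospitals turn out not to differ.
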